### Follow-up

In this study, all patients with mild-to-moderate AD will receive physical examination and skin lesion evaluation at baseline (day 0) following the enrollment, then patients will be followed up for subsequently 6 weeks and receive treatment efficacy evaluation at week 1 and week 2. The detailed information for data collection, physical examination and skin lesion evaluation is depicted in Figure 1.

### Outcomes

#### Primary outcome

The primary outcome indicator in this study is the EASI50 achievement rate at week 2. The EASI50 achievement rate is defined as the proportion of patients with mild-to-moderate AD who achieved ≥50% improvement in EASI score from baseline to week 2.

The EASI score includes the affected body surface area score (A) and clinical features score (B) of the head and neck, trunk, upper limbs, and lower limbs (19). (A) involves evaluating the percentage of affected body surface area (BSA) for each part. The percentage of affected BSA for each region is scored on a scale of 0–6: 0 (0%), 1 (<10%), 2 (10–19%), 3 (20–49%), 4 (50–69%), 5 (70–89%), and 6 (90–100%). (B) assesses four key clinical features, including erythema (E), edema/papules/infiltration (I), excoriation (Ex), and lichenification (L). Each feature is scored based on severity, ranging from 0 to 3 points (0 = none, 1 = mild, 2 = moderate, 3 = severe). The EASI score is calculated by multiplying the product of (A) and (B) with regional weighted coefficient (0.1–0.4) and then summing across all regions. The total score of EASI ranges from 0 to 72 points, with higher scores indicating greater severity. According to the EASI score, the skin lesion condition of AD patient is considered as mild (0–7 points), moderate (7–21 points), or severe (>21 points). In this study, the EASI score will be estimated at baseline (week 0), week 1, week 2, and week 6.

#### Secondary outcomes

The secondary outcome indicators include the EASI and Numerical Rating Scale (NRS) evaluated at week 1, 2, and 6; Investigator’s Global Assessment (IGA), Dermatology Life Quality Index (DLQI) and Atopic Dermatitis Control Tool (ADCT) evaluated at weeks 1 and 2 (20, 21). The comprehensive study schedule is detailed in Table 2, demonstrating the specific evaluation time-point for each indicator.

**Table 2 tab2:** Study schedule of the Fuzhiqing ointment clinical trial (6 weeks).

Indicator	Baseline	Treatment		Follow-up
	Visit 1 (week 0)	Visit 2 (week 1)	Visit 3 (week 2)	Visit 3 (week 6)
Informed consent	✓	—^a^	—	—
Demographic features	✓	—	—	—
Medical history	✓	—	—	—
Physical examination	✓	—	—	—
Blood biochemistry	✓	—	✓	—
Urine pregnancy	✓	—	✓	—
Inclusion/exclusion criteria check	✓	—	—	—
Randomization	✓	—	—	—
EASI^b^	✓	✓	✓	✓
NRS^c^	✓	✓	✓	✓
IGA^d^	✓	✓	✓	—
DLQI^e^	✓	✓	✓	—
ADCT^f^	✓	✓	✓	—
Concomitant medications	—	✓	✓	✓
Adverse events	—	✓	✓	✓

a Not applicable.

b EASI: Eczema Area and Severity Index.

c NRS: Numerical Rating Scale.

d IGA: Investigator’s Global Assessment.

e DLQI: Dermatology Life Quality Index.

f ADCT: Atopic Dermatitis Control Tool.

### NRS

Pruritus severity in patients with mild-to-moderate AD will be assessed by the validated NRS, an 11-point patient-reported instrument (0 = no pruritus, 10 = worst imaginable pruritus) (22). At each visit at baseline, week 1, week 2, and week 6, participants will assess their peak pruritus severity over the preceding 24 h using the NRS, and the NRS scores will be categorized as: 0 (none), 1–3 (mild), 4–6 (moderate), 7–8 (severe), and 9–10 (very severe).

### IGA

IGA is a validated 6-point ordinal scale enabling rapid clinical evaluation of disease severity (23). Dermatologists assess key features of skin lesion by using the following criteria: 0 = clear (no erythema), 1 = almost clear (minimal erythema; barely perceptible edema/papules), 2 = mild (mild erythema; palpable edema/papules), 3 = moderate (moderate erythema; evident edema/papules), 4 = severe (severe erythema; marked edema/papules), and 5 = very severe (confluent erythema with edema). IGA scores will be evaluated at baseline, week 1, and 2.

### DLQI

DLQI is a validated instrument that systematically evaluates health-related quality of life impairment across six domains over the preceding week, including physiological response, psychological feeling, family, interpersonal communication, occupational restrictions, social activities, and treatment response (24). Using a 4-point severity scale (0 = none, 1 = mild, 2 = severe, 3 = very severe) for each of 10 items, the DLQI score is obtained by summing up the scores of each items, which ranges from 0 to 30, with higher score indicating greater quality of life impairment. The DLQI assessments will be conducted at baseline, week 1 and 2.

### ADCT

ADCT is an important tool for AD patients to self-evaluating their disease control status. It can assess both the severity of the disease and the quality of life of patients over the past week, achieving a comprehensive evaluation of the effectiveness of AD control. It includes overall symptom severity score, number of severe itching episodes, discomfort, sleep disorders, and the impact of AD on daily life and emotions, covering multiple dimensions of long-term control. Each item is scored on a 0–4 scale (0 = none, 1 = mild, 2 = moderate, 3 = severe, 4 = very severe), with total scores ranging from 0 to 24 points. The ADCT score below 7 indicates that the disease is under control for AD patients. It will be evaluated at baseline, week 1 and 2.

### Safety assessment

In this study, patients with mild-to-moderate AD will be informed of the risks that may arise in the study before signing the informed consent form. We define adverse events as unintended signs, symptoms, or diseases occurring after treatment that are not necessarily related to the intervention. The occurrence of any adverse events will be accurately recorded in the CRF. In this study, appropriate treatment will be provided by dermatologists when encountering adverse events, the adherence condition of AD patients and the adverse events will be recorded. Meanwhile, liver and kidney function test for all participants and urine pregnancy test only for female participants will be conducted at baseline and week 2 for safety evaluation.

### Withdraw and dropout

According to the declaration of Helsinki, all participants will be respected and can withdraw from the study at any time for any reason. Personal information of participants will be collected and kept confidential. In this study, patient can withdraw at any time, and the reason for withdrawal will be recorded in the case report form (CRF).

### Data collection and management

Trained dermatologists will collect data using standardized case report form (CRF). The CRF comprises six sections: (1) demographic feature: age, gender, and census register; (2) diseases history of AD; (3) physical examination for height, weight and body mass index (BMI); (4) EASI, NRS, IGA, DLQI, and ADCT score recorded at baseline, week 1, 2, and 6; (5) liver and kidney function test for all participants and urine pregnancy test only for female participants; (6) prior drug history, concomitant medications, and adverse events.

We will establish a dedicated Data Monitoring Committee responsible for regularly reviewing the data collected throughout the study to ensure its accuracy and completeness. Adverse events will be reported according to the predefined protocol and reviewed by independent monitoring personnel. Data monitoring will involve real-time tracking and periodic summaries to ensure the early detection of potential issues.

The database will be constructed in Epidata 3.1 software with comprehensive validation rules. Data for all 210 participants will be entered using the double data entry method by two independent operators. Subsequent consistency checks between both datasets will identify discrepancies, and all inconsistencies will be resolved against source documents (original CRF) through iterative verification until 100% concordance is achieved.

### Statistical analysis

In this study, analysis will be performed by applying SAS 9.4 statistical package. Normally distributed quantitative variables will be summarized as mean and standard deviation (SD), while those with skewed distributions will be presented as median and interquartile range (IQR). The Student *t*-test will be used for inter-group comparison of quantitative variables with normal distribution, while the Wilcoxon rank-sum test will be employed for quantitative data with skewed distribution. The repeated measurement data will be analyzed by repeated measure analysis of variance. Categorical variables will be reported as frequencies and proportions (%), with group differences assessed using chi-square tests or Fisher’s exact tests. In this study, data analysis will adhere to the intention-to-treat (ITT) principle, including all randomized patients regardless of protocol adherence or study completion (25). Missing data will be handled under the missing-at-random assumption using sequential regression multiple imputation, which imputes missing values through regression models for each variable conditional on the other variables (26). Additionally, data analysis will be conducted on both the full analysis set (FAS) and the per-protocol set (PPS), and a *p*-value less than 0.05 (two tailed) is considered as statistically significant.

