**Methods and analysis:**

A total of 210 patients with mild-to-moderate AD will be recruited from 10 hospitals across China between September 2025 and February 2026. Participants will be randomly assigned in a 2:1 ratio to receive either the treatment (urea vitamin E cream combined with Fuzhiqing ointment; *n* = 140) or the control (urea vitamin E cream combined with placebo Fuzhiqing ointment; *n* = 70). Both groups will apply the treatments twice daily for 2 weeks, followed by a 4-week observational follow-up period. The primary outcome will be the proportion of patients achieving ≥50% improvement in the Eczema Area and Severity Index (EASI) score at week 2 (EASI_50_). Secondary outcomes will include changes in the EASI, Numerical Rating Scale (NRS), Investigator’s Global Assessment (IGA), Dermatology Life Quality Index (DLQI), and Atopic Dermatitis Control Tool (ADCT) at weeks 1 and 2, as well as the EASI, NRS, and adverse events at week 6. Statistical analyses will be performed using SAS 9.4, with significance defined at a two-tailed *α* level of 0.05.

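### The methods named for the secondary scores include no baseline covariate, although every score is measured at baseline; adjusting for it would give more precise estimates at almost no cost

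*Protocol article*

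**What the plan says.** The Statistical analysis section of the protocol article gives three methods that could apply to the secondary scores.

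- A Student t procedure for variables judged normal: this "test will be used for inter-group comparison of quantitative variables with normal distribution".
- A rank test for the others: "the Wilcoxon rank-sum test will be employed for quantitative data with skewed distribution".
- For repeated data: "The repeated measurement data will be analyzed by repeated measure analysis of variance".

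It names no baseline covariate, analysis of covariance or mixed model, and does not say whether baseline is a level of the repeated-measures ANOVA.

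Baseline values exist for every scale. For EASI, "the EASI score will be estimated at baseline (week 0), week 1, week 2, and week 6". NRS is recorded "At each visit at baseline, week 1, week 2, and week 6". The IGA, DLQI and ADCT sections and Table 2 show baseline, week 1 and week 2.

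The analysed variable is worded in two ways. The Secondary outcomes section lists scores by visit: "The secondary outcome indicators include the EASI and Numerical Rating Scale (NRS) evaluated at week 1, 2, and 6". The abstract speaks of changes: "Secondary outcomes will include changes in the EASI, Numerical Rating Scale (NRS" and the remaining scales.

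**The concern.** A patient's baseline score usually predicts the later score. A two-sample t-test or rank-sum test on the later score cannot use that information. A test on the change uses it with a fixed slope of 1, which is rarely the best slope. With the baseline score as a covariate, the data choose the slope and the residual variance falls.

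At stake is the width of the confidence intervals for EASI, NRS, DLQI and ADCT. These scores carry the evidence on mean severity, itch and quality of life beyond the binary primary outcome, and there are only 70 controls. The data needed for the better analysis are already being collected.

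**Working it through.** The article gives no figure on the precision of the secondary scores, so there is none to reproduce. Its sample size calculation concerns EASI50 and plays no part here.

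**Inputs from the article:** 140 and 70 patients (Sample size), two-sided alpha 0.05 (Statistical analysis), and baseline measured for every score (Table 2).

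**Inputs assumed:** correlation r between baseline and the visit of 0.3 to 0.7, since the article gives none; the same SD s at baseline and at the visit, and in both arms.

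**Variance of the single-visit treatment difference.** Each analysis has its per-patient variance multiplied by the same factor, 1/140 + 1/70 = 0.0214, so ratios depend only on the per-patient variance:

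- score at the visit: s²
- change from baseline: 2s²(1 − r)
- ANCOVA: s²(1 − r²)

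ANCOVA relative to the score is therefore 1 − r². Relative to the change it is (1 − r²) / [2(1 − r)] = (1 + r)/2.

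| r | ANCOVA / score | reduction | ANCOVA / change | reduction |
|---|---|---|---|---|
| 0.3 | 0.91 | 9% | 0.65 | 35% |
| 0.5 | 0.75 | 25% | 0.75 | 25% |
| 0.7 | 0.51 | 49% | 0.85 | 15% |

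The two reductions move in opposite directions: where adjustment gains little over the score, it gains most over the change. ANCOVA has the smaller variance than either for every r strictly between 0 and 1.

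**Power.** Take the effect with 80% power under a t-test on the score: (1.960 + 0.842) × √0.0214 = 0.41 SD. With v the per-patient variance in units of s², power is Φ(2.802/√v − 1.960).

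| r | score | change | ANCOVA | unadjusted score trial of equal precision |
|---|---|---|---|---|
| 0.3 | 80% | 65.8% | 83.6% | 210/0.91 = 231 |
| 0.5 | 80% | 80.0% | 89.9% | 210/0.75 = 280 |
| 0.7 | 80% | 95.1% | 97.5% | 210/0.51 = 412 |

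**Simulation check** (normal data, 140/70, 2,000 runs per setting). For r = 0.3, 0.5 and 0.7, power was 0.79, 0.80, 0.79 for the score; 0.64, 0.80, 0.95 for the change; and 0.81, 0.90, 0.97 for ANCOVA. With no treatment effect, rejection rates lay between 4.7% and 5.7% for all three analyses.

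**Link to the repeated-measures ANOVA.** With two visits, baseline and one later, the group-by-time test equals the t-test on change, so the change column applies. With more visits the comparison depends on the visits included and the contrast reported, which the article does not give. The figures above are therefore for a single visit such as week 2.

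**The case against.** The strongest reply is that model terms belong in the statistical analysis plan or full protocol, neither of which is shown, and that an article's silence on covariates is no error. This stands for the ANOVA, which could be given a covariate there. It does not cover the t-test and the rank-sum test, which the article names outright and which take no covariate.

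It is also fair that the gain rests on an assumed correlation and can be small: at r = 0.3 it is 9% of the variance against the score, or 83.6% power instead of 80%.

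A reader might infer more than the article supports:

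- *Baseline is thrown away.* Not so if changes are analysed, as the abstract says, or if baseline is a level of the ANOVA. It is then used, only less efficiently.
- *Each scale is tested twice, with the test picked after looking at the data.* No normality pre-test is stated, and no scale is assigned to both routes. A natural reading sends the repeated scores to the ANOVA and leaves the t-test and Wilcoxon test for variables such as age or BMI. The overlap is a possible ambiguity.
- *The ANOVA dilutes the effect by a quarter for EASI and NRS.* This needs baseline as one of four levels, equal effects at weeks 1, 2 and 6, and inference from the group main effect. The article states none of these, and the group-by-time interaction is not diluted in this way.
- *Sphericity is violated.* IGA, DLQI and ADCT have two post-baseline visits, where sphericity holds automatically unless baseline is added as a level. For EASI and NRS a correction is a detail for the analysis plan.

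**Conclusion.** The point holds as one of efficiency. Naming the baseline score as a covariate is a better method than those stated. For r from 0.3 to 0.7 it lowers the variance of a single-visit treatment difference by about 9–49% against the score and 15–35% against the change.

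The exact sizes rest on the assumed correlation and on equal SDs. The direction does not rest on equal SDs: the fitted slope minimises the residual variance, so a fixed slope of 0 (score) or 1 (change) cannot do better, apart from one degree of freedom.

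The documents do not support calling the planned analyses invalid. Each unadjusted test keeps its type I error near 5%, and EASI50 at week 2 and its sample size are untouched. The change is worth making because it is nearly free, not because it repairs an error.

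**What to change.** Before unblinding, name one baseline-adjusted analysis for each of EASI, NRS, DLQI and ADCT. Either of these will do:

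- ANCOVA at week 2 with treatment, baseline score and hospital; or
- a mixed model for repeated measures on the post-baseline visits, with treatment, visit, treatment-by-visit, baseline score and hospital.

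In both cases report the week-2 adjusted mean difference with its 95% confidence interval, and keep the Wilcoxon test as a sensitivity analysis. An ordinal model for IGA, adjusted for baseline, is optional.

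One further decision is needed. The Statistical analysis section already plans sequential regression multiple imputation under missing at random, and a likelihood-based mixed model handles missing outcomes under the same assumption. The text should say whether the chosen analysis is run on the imputed data or replaces imputation for these scores.

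The cost is a few sentences in the Statistical analysis section. SAS 9.4, already named there, fits both models. No new patients, visits or measurements are needed, and the article puts the start of analysis in May 2026.

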### Sample size

The sample size was calculated based on the EASI50 achievement rate at week 2, which was defined as the proportion of patients who achieved ≥50% improvement in Eczema Area and Severity Index (EASI) score from baseline to week 2. According to previous evidence, we assume that the EASI50 achievement rate at week 2 was 60% in the treatment group and 30% in the control group (18). The sample size calculation for a 2:1 randomization design performed in PASS 15.0 (NCSS Statistical Software) indicates that 116 patients in the treatment group and 58 patients in the control group need to recruit with a 2-tailed *α* level of 0.05 and a statistical power of 80%. Considering a dropout rate of 10 and 10% multicenter effect, the final enrollment targets are 140 patients in the treatment group and 70 patients in the control group.

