### Randomization

In this study, a total of 210 patients with mild-to-moderate AD will be randomly allocated to either treatment group or control group in a 2:1 ratio. We will apply cluster randomization with the combined blocks of 4 and 6 to ensure a balanced group allocation. Randomization sequences will be computer-generated by an independent statistician using SAS software (version 9.4; SAS Institute Inc). Randomization was centralized across all 10 hospitals, with 21 random numbers assigned to each hospital. Allocation concealment will be maintained through sequentially numbered, opaque envelopes securely stored with restricted access at the clinical research center of Shanghai Skin Disease Hospital.

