This study is subject to several limitations. First, participant recruitment is restricted to individuals with mild-to-moderate AD, enhancing internal validity while potentially limiting the generalizability of findings to broader populations. Second, the protocol mandates a 2-week active treatment phase followed by a 4-week observational follow-up period, which limits the observation of long-term effects of Fuzhiqing ointment, as well as its efficacy of diseases recurrence prevention in patients with AD. Third, differences of climate (temperature, humidity, ultraviolet radiation, seasonal changes), lifestyle habits (high-fatty food consumption, high-calorie diets, tobacco smoking, alcohol drinking) and other extrinsic factors (cultural difference, occupational exposure, etc.) in the 10 selected hospitals may cause information bias. Fourth, patients in this study will be instructed not to use any additional treatment for AD which might induce a relatively high rate of withdrawal.

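### The stated test for EASI50 ignores hospital although random numbers are assigned by hospital; with near-balance inside hospitals it is mildly conservative and gives up a little power

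*Protocol article*

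**What the plan says.** - **Primary outcome:** "The primary outcome indicator in this study is the EASI50 achievement rate at week 2", a yes/no result for each patient.
- **Statistical analysis:** one rule covers all categorical variables. They are reported as frequencies and proportions, "with group differences assessed using chi-square tests" or Fisher's exact test, and a p-value "less than 0.05 (two tailed) is considered as statistically significant". No stratum, centre term or adjusted model is named.
- **Randomization:** patients are allocated 2:1, centrally, "with 21 random numbers assigned to each hospital". The section also calls the scheme cluster randomization and uses blocks of 4 and 6.
- **Sample size:** the target is raised "Considering a dropout rate of 10 and 10% multicenter effect".
- **Discussion, limitations:** differences in climate, lifestyle and other external factors "in the 10 selected hospitals may cause information bias".

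**The concern.** Three parts of the article treat hospital as something that matters: allocation, sample size and limitations. The named test then pools all patients as if hospital did not exist. This is a stated choice and not a gap, because the test is named and it has no place for hospital.

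If allocation is balanced within hospitals, differences in response between hospitals largely cancel out of the treatment comparison. The pooled chi-square still counts those differences in its variance. The variance is then too large, the true type I error falls below 5%, and some power is lost. At stake is efficiency in the primary analysis, and agreement between the analysis and the way patients are allocated.

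**Working it through.** **Inputs from the protocol article**
- "EASI50 achievement rate at week 2 was 60% in the treatment group and 30% in the control group"; two-sided "level of 0.05 and a statistical power of 80"%.
- 116 + 58 patients before inflation, 140 + 70 after it.
- 10 hospitals with 21 numbers each. At 2:1 that is 14 treatment and 7 control per hospital.

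**Assumed, not in the documents**
- The between-hospital SD of response on the logit scale, shown as a range.
- A smaller true effect of 50% versus 30%.

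**1. The plan's own sample size.** With pooled variance and k = 2 treated patients per control:

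n_c = [1.96·√((1 + 1/k)·p̄(1 − p̄)) + 0.8416·√(p_c(1 − p_c) + p_t(1 − p_t)/k)]² / (p_t − p_c)²

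- p̄ = (2 × 0.6 + 0.3)/3 = 0.5.
- The first term is 1.96·√0.375 = 1.200. The second is 0.8416·√0.33 = 0.483.
- n_c = 1.684²/0.09 = 31.5, so 32 control and 64 treatment (37 and 74 with continuity correction).

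The stated 58 and 116 do not reproduce. They give about 97.0% power, and 70 and 140 give about 98.9%. The inflation step does reproduce: 116 × 1.2 = 139.2 → 140 and 58 × 1.2 = 69.6 → 70. The mismatch is a separate matter. It is relevant here only because it leaves the trial with far more than 80% power at the planned rates.

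**2. Why pooling is conservative.** The pooled variance uses P(1 − P), which equals the average within-hospital p_h(1 − p_h) plus the variance of p_h between hospitals. With 14:7 everywhere the second part drops out of the treatment difference but stays in the standard error.

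**3. Simulation.** Ten hospitals of 14:7, normal hospital effects on the logit scale, overall rates held at the stated values, 40,000 trials per setting. The Cochran-Mantel-Haenszel (CMH) statistic sums a_h − E_h over hospitals and divides by √ΣV_h. With m_h responders in a hospital, E_h = 14m_h/21 and V_h = m_h(21 − m_h)·14·7/(21²·20).

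| Hospital SD | Type I error, chi-square / CMH | Power 60% v 30%, chi-square / CMH | Power 50% v 30%, chi-square / CMH |
|---|---|---|---|
| 0 | 5.1% / 5.0% | 98.7% / 98.7% | 80.5% / 79.9% |
| 0.5 | 4.7% / 5.1% | 98.9% / 99.1% | 81.1% / 82.1% |
| 0.75 | 4.1% / 5.0% | 99.1% / 99.4% | 81.5% / 84.0% |
| 1.0 | 3.4% / 4.8% | 99.2% / 99.6% | 81.8% / 86.2% |

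A separate run at SDs of 0.5, 0.8 and 1.0 gave chi-square type I errors of 4.5%, 3.9% and 3.4%. The two sets differ by no more than simulation noise.

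**4. Cross-check on the standard error.** Under the null at SD 1.0, the unstratified SE of the risk difference averages 0.0660 and the true sampling SD is 0.0614, a ratio of 1.075. The effective critical value is 1.96 × 1.075 = 2.107, which has two-sided tail probability 3.5%. That agrees with the simulated 3.4%.

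**5. Dependence on the allocation scheme.**
- A block of 4 cannot hold 2:1, since 4 × 2/3 is not a whole number.
- 21 is odd, so it cannot be a sum of 4s and 6s. Exact 14:7 is therefore not guaranteed.
- If treatment were not balanced by hospital at all, the chi-square type I error would be about 5% at every SD and the conservatism would vanish.
- If whole hospitals were allocated, the error would run the other way. The design effect would be 1 + 20 × ICC, which is 2.0 at an assumed ICC of 0.05.

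**The case against.** The strongest reply is that the practical loss is very small. At the protocol's own 60% versus 30%, power is about 99% with either test. If the planned odds ratio of 3.5 is instead held fixed within hospitals, so that the overall difference shrinks as hospitals vary, the loss is still only about 0.2 to 1.7 points for SDs of 0.5 to 1.0. This stands, and it limits the weight of the point.

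The hospital SD is also unsupported. The article gives no response rates by hospital, eligibility is narrow (under 10% of body surface, age 18 to 60), and EASI50 is a change within the patient. An SD of 1.0 corresponds to a latent-scale ICC of about 0.23, which is large. This stands too, so the figures are a range and not an estimate.

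Extra patients can be seen as a legitimate way to offset an unadjusted analysis. That is fair, but using hospital in the analysis recovers the efficiency without recruiting anyone.

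A reader might also infer that the article should say how imputed datasets are pooled, or that its confidence intervals are too wide. The documents do not support either as a finding. The article states no interval method for EASI50, a risk difference with a standard error follows from the reported proportions, and pooling rules are commonly left to the analysis plan, which is not shown.

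**Conclusion.** The point holds as a modest improvement to a stated method. The primary test ignores a factor used in allocation. Under patient-level 2:1 randomisation with near-balance within hospital, and with real differences between hospitals, the pooled test is conservative: about 4.5% to 3.4% against a nominal 5% for assumed SDs of 0.5 to 1.0. The power cost is under 1 point if 60% and 30% are the overall rates, and about 1 to 4 points at 50% versus 30%. With no hospital variation the tests agree.

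Two stronger readings are tempting. One is that the trial loses power that matters at its planned effect; the protocol's own rates do not bear this out. The other is that ignoring hospital inflates false positives. That would follow only if whole hospitals were allocated. The phrase cluster randomization invites that reading, but 2:1 allocation of patients, blocks, and a set of numbers for each hospital point to randomisation within hospitals. The direction of the error rests on that interpretation, so the Randomization section needs correcting along with the test.

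**What to change.** 1. In Statistical analysis, before unblinding, name the primary analysis of EASI50 as a Cochran-Mantel-Haenszel test stratified by hospital, or a logistic regression with treatment and hospital. Report the hospital-stratified risk difference with its 95% CI. Keep the unadjusted chi-square as a sensitivity analysis.
2. In Randomization, replace the cluster wording with patient-level randomisation stratified by hospital, and reconcile the block sizes with the 2:1 ratio and the 21 numbers per hospital so that the text describes the scheme actually used.

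The cost is a sentence or two of wording. Hospital is already known from allocation, so no new data are needed. If hospitals turn out not to differ, stratifying costs about half a point of power (80.5% versus 79.9% at 50% versus 30%). Data analysis is planned to start in May 2026, so the change should be dated and fixed before then.
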